## Abstract

**Background:**

Pancreatic ductal carcinoma (PDAC) is the fourth most frequent cause of cancer-related death in the Western world, and its incidence is rising. In patients that undergo curative resection, local recurrence (LR) is frequent. A recently described surgical technique of extended pancreatoduodenectomy (PD) termed the TRIANGLE operation has been proposed as a promising approach to reduce LR and improve disease-free survival in PDAC patients.

**Methods:**

The TRIANGLE trial is a multicentre confirmatory randomised controlled superiority trial with two parallel study groups. A total of 270 patients with suspected or histologically confirmed pancreatic head cancer scheduled for PD will be included in the trial and randomly assigned to the intervention group (extended PD defined as Inoue level 3 dissection along the superior mesenteric and celiac artery as well as removal of all soft tissue in the so-called triangle between the celiac artery, the SMA and the mesenterico-portal axis) or the control group (conventional PD with lymphadenectomy and removal of soft tissue according to current guidelines). The primary endpoint of the trial will be the disease-free survival of patients. Other perioperative outcomes as well as oncological parameters and patient-reported outcomes will be analysed as secondary outcomes.

**Discussion:**

Despite multimodal treatment, LR remains high and disease-free survival is limited following PD for PDAC. The TRIANGLE operation could address these shortcomings of conventional PD as indicated in several retrospective studies. However, this technique could be associated with more adverse events for patients including intractable diarrhoea. The TRIANGLE trial will close the evidence gap as well as offer a risk-benefit assessment of this more radical approach to PD.

**Trial registration:**

German Clinical Trials Register DRKS00030576 (UTN U1111-1243-4412) 19th December 2022.

**Supplementary Information:**

The online version contains supplementary material available at 10.1186/s13063-023-07337-6.

## Administrative information

Note: The numbers in curly brackets in this protocol refer to the SPIRIT checklist item numbers. The order of the items has been modified to group similar items (see http://www.equator-network.org/reporting-guidelines/spirit-2013-statement-defining-standard-protocol-items-for-clinical-trials/).

## Introduction

### Background and rationale {6a}

Pancreatic ductal adenocarcinoma (PDAC) is the fourth most frequent cause of cancer-related death in the Western world, and its incidence is rising [1, 2]. Survival differs widely depending on the tumour stage and surgical resection via pancreatoduodenectomy (PD) in case of tumours of the pancreatic head is one of the mainstays in the treatment of PDAC and the only option for curative treatment [3–5]. The rise of more efficient chemotherapeutic regimes like FOLFIRINOX or Gem/nabPac in recent years, has led to an increased use of neoadjuvant treatments raising the hope that more patients will qualify for potential curative resection in the future [6].

However, local recurrence (LR) is frequent following surgical resection for PDAC, and prognosis is significantly worse for patients experiencing LR compared to non-LR [7].

Several independent risk factors predict LR, one of which is the status of the pathological resection margin. The R0 resection rate has been proposed as a quality indicator for pancreatic surgery [8, 9] and has shown to be an important prognostic parameter not only for local recurrence but can also improve overall survival (OS) as well as disease-free survival (DFS) in PDAC patients [10].

Owing to the perineural growth pattern of PDAC, R1 resections occur most frequently along the soft tissue margins towards the celiac and superior mesenteric artery (i.e. medial margin) [11, 12]. Therefore, by applying more radical dissection techniques along the superior mesenteric artery (SMA) and the celiac artery (CA), marginal clearance can be improved.

Concerning the radicality around the SMA, Inoue et al. have proposed a classification system including 3 levels of dissection around the SMA [13]. A recently proposed surgical technique goes beyond level 3 SMA dissection by additionally resecting all soft tissue between the CA, the SMA and the mesenterico-portal axis (MPA) (the so-called triangle) [14, 15]. This operation leads to clearance of all soft and lymphatic tissue which drains the pancreatic head and seems a promising approach as LR following PDAC resection frequently occurs in the “triangle” region between CA, SMA and MPA [16–18]. In addition, the R0 status along the posterior and medial margins has been associated with improved local recurrence and DFS in a recent study [19]. Consequently, the TRIANGLE operation has the potential to improve LR and DFS following PD surgery for pancreatic head cancer [10, 13]. However, high-quality data in terms of a multicentre randomised controlled trial are lacking so far. Therefore, the TRIANGLE trial aims to evaluate whether the “TRIANGLE” operation increases DFS in patients with carcinomas of the pancreatic head.

### Objectives {7}

The TRIANGLE trial aims to evaluate whether a more radical dissection along the SMA and removal of all lymphatic and soft tissue between the CA, the MPA and the SMA (the so-called triangle) during PD in comparison with conventional PD increases DFS in patients with carcinomas of the pancreatic head.

### Trial design {8}

The TRIANGLE trial is a multicentre confirmatory randomised controlled patient and outcome assessor blinded superiority trial with two parallel study groups.

## Methods: participants, interventions and outcomes

### Study setting {9}

The trial will be carried out in at least seven pancreatic cancer centres. Most of the centres are part of the Clinical Trial Network of the German Society of Surgery (CHIR-Net; www.chir-net.de). A list of the trial sites can be found in Additional file 1.

### Eligibility criteria {10}

The following are the preoperative inclusion criteria for patients:Patients with suspected or histologically verified resectable, borderline or locally advanced pancreatic cancer of the pancreatic head (i.e. pancreatic ductal adenocarcinoma, intraductal papillary mucinous neoplasm (IPMN)-carcinoma or periampullary cancer of the pancreatobiliary-type)Patients scheduled for elective partial pancreatoduodenectomy (irrespective of neoadjuvant therapy)Assumed resectability in accordance with the surgical protocol for experimental and control intervention as judged by the treating surgeonAbility of the subject to understand character and individual consequences of the clinical trialWritten informed consentAge ≥ 18 years

The following are the intraoperative inclusion criteria for patients (prior to randomisation):No distant metastasesNo paraaortic lymph node metastasesIntraoperative confirmation that the patient can be operated on according to both surgical methods (experimental or control group)

The following are the exclusion criteria for patients:Participation in another interventional trial with the interference of intervention and outcome of this trialAmerican Society of Anesthesiologists (ASA) grade > 3Distant metastatic disease

### Eligibility criteria for trial centres

All participating trial sites will be high-volume centres with broad expertise in pancreatic surgery and have the necessary expertise, equipment and personnel to perform this trial.

### Who will take informed consent? {26a}

All patients scheduled for PD will be screened preoperatively with regard to the inclusion and exclusion criteria. An authorised investigator will inform the patient, orally and written, about the aims of the trial, the possible risks, the procedures, the possible hazards to which he/she will be exposed and the mechanism of treatment allocation (randomisation). The written informed consent form will be signed and personally dated by the patient according to the ICH guidelines in Good Clinical Practice.

### Additional consent provisions for collection and use of participant data and biological specimens {26b}

No additional biological samples will be collected during the trial.

### Interventions

#### Explanation for the choice of comparators {6b}

As outlined in the introduction, radical extended PD including the removal of the tissue in the TRIANGLE area could improve the R0 resection rate and thereby the survival of patients suffering from pancreatic cancer. So far, high-quality data in terms of a multicentre randomised controlled trial on the TRIANGLE intervention are lacking. Therefore, a trial evaluating the effect of the TRIANGLE intervention compared to standard PD according to the current guidelines is needed.

#### Intervention description {11a}

##### Exploration phase (experimental and control group)

The experimental intervention is limited to the resection phase. Thus, both groups (experimental and control) start with the same exploratory phase. After safe access to the abdominal cavity, the exploration phase should comprise the following steps, which can be performed in any order (at the discretion of the surgeon):Exclusion of hepatic metastases and peritoneal carcinomatosis. If distant metastases are present, the patient must not be randomised.Dissection of the gastrocolic ligament to open the lesser sack and define tumour extent along the pancreatic gland and the stomach. No transection is performed at this time.Any type of artery-first approach may be performed to explore potential tumour infiltration [20]. If resection of the tumour is not possible based on intraoperative findings, the patient must not be randomised.A Kocher manoeuvre is performed to expose the para-aortic lymph nodes (LNs) and the root of the SMA.If a suspicious para-aortic LN is detected, it should be resected and sent for frozen section.In case the frozen section procedure reveals tumour infiltration, no randomisation should be performed as available data shows that the prognosis of patients with positive para-aortic LNs is poor (ISGPS guidelines [21]).After the exclusion of distant and paraaortic LN metastases and intraoperative confirmation that the patient can be operated according to both experimental or control groups, randomisation will be performed.

##### Resection phase—experimental group (TRIANGLE operation)

The experimental intervention consists of two parts:ADissection of the SMA according to level 3 described by Inoue et al. [13]. This step includes a dissection of the nerve plexus around the superior mesenteric artery (plSMA) from at least 5 to 11 o’clock (180°). A wider resection (≥ 180°) up to a circular (360°) resection of the lymph plexus and plSMA is allowed and at the discretion of the surgeon. Performing this step should result in a circular (360°) dissection of the superior mesenteric vein (SMV).BComplete dissection of the soft tissue in the “triangle” between CA, SMA and MPA [14].

##### Resection phase—control group

Patients randomised to the control group will receive standard PD with dissection of the SMA according to Inoue level 1 or 2 and standard lymphadenectomy according to the German S3 guidelines [8] but no TRIANGLE operation. This constitutes the current standard of care.

Deviations from the described control intervention with venous or arterial reconstruction or extended pancreatectomy in case of advanced tumour infiltration are possible as long as there is no radicality necessary according to Inoue level 3 along the SMA or removal of soft tissue in the triangle area.

##### Resection phase—experimental and control groups

The further key steps of the resection phase in the experimental as well as the control group should include lymphadenectomy in the hepatoduodenal ligament as described in the German S3 guidelines [8]. Furthermore, the transected end of the bile duct and the transection of the pancreatic body should be sent for frozen section to rule out microscopic tumour infiltration. In case of tumour infiltration in the pancreatic body, further resection of the pancreatic body is indicated. Transection of the postpyloric duodenum or the prepyloric stomach should be performed as oncologically necessary. Therefore, pylorus-preserving, pylorus-resecting or classical Whipple procedures or any variants are allowed in the trial. If extended pancreatic resections (e.g. total pancreatectomy) or resection of neighbouring organs are necessary, patients remain in the trial. Details should be given during visit 2 (surgery). Any kind of venous or arterial resection and reconstruction can be performed as deemed necessary by the operating surgeon.

##### Reconstruction phase—experimental and control groups

The reconstruction phase is the same in both groups including pancreatojejunostomy or pancreaticogastrostomy, hepaticojejunostomy and a duodeno- or gastrojejunostomy according to local standards. Similarly, the placement of drains, abdominal wall and skin closure should be performed according to local standards. Details will be recorded during visit 2.

If reconstruction needs to be performed later in a second operation, this is possible and does not result in the exclusion of the patient from the trial.

### Criteria for discontinuing or modifying allocated interventions {11b}

After inclusion into the trial, patients still have to meet the intraoperative inclusion criteria to be finally randomised to one of the intervention groups. If during the exploration phase distant metastases or paraaortic lymph node metastases are found or it can not be confirmed that the patient can be operated on according to both surgical methods (experimental or control group), the patient has to be excluded intraoperatively and will be defined as an intraoperative drop-out. Furthermore, if, in the investigator’s opinion, continuation of the trial intervention would be detrimental to the subject’s well-being, the investigator may stop the trial intervention for this patient. In this case, the reason for the individual premature trial termination must be recorded in the electronic case report form (eCRF) and in the patient’s medical records.

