Intervention effect: Possible intercurrent events and the strategies to handle them are as follows: Death, as an intercurrent event occurring after randomisation, is handled by inclusion into the definition of the primary endpoint which reflects a composite strategy. Patients with incomplete observation time due to loss to follow-up or early drop-out will be censored at the last observation, which reflects a hypothetical strategy. Besides these events, other post-randomisation events (e.g. intervention not as randomised, discontinuation of chemotherapy) will not be considered, thus reflecting a treatment policy approach, which means that the effect of randomised treatment is estimated irrespectively of other post-randomisation events not captured in the primary endpoint definition. This corresponds to the intention-to-treat (ITT) principle.

Summary measure: The summary measure is the adjusted hazard ratio.

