**Fig. 1 Fig1:**
[figure not shown]
Flow chart of the TRIANGLE trial. F/U, follow-up; POD, postoperative day; PD, partial pancreaticoduodenectomy; R, randomisation. *Respective visits are skipped if the patient has been discharged before

**Table 2 Tab2:** Trial visits and documented parameters

**Visit**	**1**	**2**	**3–4**^a^	**5**	**6**	**7–12**
**Time point**	Screening	Day of surgery, pathology	POD 5 POD 10–12	Day of discharge	POD 90	POM 6, 12, 18, 24, 30, 36 (or pre-mature trial termination)
**Type of visit**	Inpatient	Inpatient	Inpatient	Inpatient	Outpatient (inpatient) (telephone)	Outpatient (telephone)
Written informed consent	**X**					
Preoperative inclusion/exclusion criteria	**X**					
Intraoperative inclusion criteria		**X**				
Demographics and baseline data	**X**					
Medical history	**X**					
Surgery data		**X**				
Randomisation		**X**				
*Primary endpoint*						
Disease-free survival			**X**	**X**	**X**	**X**
*Secondary endpoints*						
Pathologic data		**X**				
Postoperative morbidity			**X**	**X**	**X**	
Length of hospital stay				**X**		
Overall survival			**X**	**X**	**X**	**X**
Local recurrence			**X**	**X**	**X**	**X**
*Patient-reported outcomes (PRO)*						
Quality of recovery^c^	**X**		**(X)**^d^			
Quality of life assessment^b^	**X**			**X**		**X**
*Safety*						
SAE		**X**	**X**	**X**	**X**	**X**

*POD* Postoperative day, *POM* Postoperative month, *PRO* Patient-reported outcome, *SAE* Serious adverse events

^a^Skip respective visits if the patient has been discharged prior to visit

^b^According to EORTC QLQ-C30 and -PAN26

^c^According to the QoR-15

^d^Only on POD 5

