### Sample size {14}

The sample size calculation is based on the primary endpoint disease-free survival. The assumptions are based on a median survival time of 14 months in the control group and 21 months in the treatment group resulting in a corresponding hazard ratio of 0.667 assuming exponentially distributed survival times [7, 16, 33]. To detect the assumed difference using a log-rank test at a significance level of 5% (two-sided) with a power of 80%, a total number of 192 events (i.e. recurrence or deaths) are required for the entire trial. It is expected that applying the Cox proportional hazards model, as described below, will lead to an increase in power. With an accrual period of 30 months and a follow-up period of at least 36 months, and assuming an exponentially distributed drop-out rate of 20% (at 66 months), *n* = 270 (135 per group) patients are needed (based on the approximation formula by Schoenfeld). The sample size calculation was done using ADDPLAN 6.1.1.

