## Statistical methods

### Statistical methods for primary and secondary outcomes {20a}

The primary outcome disease-free survival is compared between the groups using a Cox proportional hazards model adjusted for the covariates treatment group, age, neoadjuvant treatment, adjuvant treatment as fixed effects and centre as a random effect. It can be expected that applying the Cox proportional hazards model will lead to an increase in power in comparison with a log-rank test. Confounding by other less important prognostic and predictive factors can be assumed to be controlled by the randomised trial design. The significance level is set to 5% (two-sided). The confirmatory analysis is conducted based on the full analysis set (FAS) according to the ITT principle, i.e. all randomised patients are included and analysed in the treatment group as randomised which reflects a treatment policy approach (according to the ICH E9 (R1) addendum). Death, as an intercurrent event occurring after randomisation, is handled by inclusion into the definition of the primary endpoint which reflects a composite strategy.

All secondary outcomes will be evaluated descriptively, and descriptive *p*-values for the corresponding effects will be reported along with 95% confidence intervals. Continuous variables will be described using a number of missing values, non-missing values, mean, standard deviation, median, Q1, Q3, minimum and maximum. For binary or categorical variables, absolute and relative frequencies will be provided. Thereby, binary and categorical variables will be compared by the chi-squared tests, and continuous variables will be compared with *t*-tests. OS will be analysed analogously to the primary endpoint with a Cox proportional hazards model. QoL will be analysed using linear mixed models with baseline score, age, treatment group and the stratification variables as covariates; centre and time point will be included as random effects. Furthermore, the treatment effect for secondary endpoints will be assessed descriptively within several subgroups to identify potential prognostic and predictive factors. Analyses of secondary endpoints will be based on the ITT population. No imputation of missing values will be conducted in the analyses of secondary endpoints.

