### Methods in analysis to handle protocol non-adherence and any statistical methods to handle missing data {20c}

The confirmatory analysis of the primary endpoint will be conducted according to the ITT principle which reflects a treatment policy approach according to the ICH E9 (R1) addendum. Patients with incomplete observation time due to loss to follow-up or early drop-out will be censored at the last observation (hypothetical strategy). Further post-randomisation events will be ignored. This also reflects a treatment policy approach. Because of the use of the Cox approach, no missing values in the primary endpoint will occur. Furthermore, no missing values in the covariates of the Cox model are expected.

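### Stopping the operation after randomisation is called premature trial termination, which opens a route to early censoring that the treatment-policy estimand does not allow

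*Protocol article*

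**What the plan says.** Section {11b} covers two situations.

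- **Before randomisation.** A patient who fails an intraoperative criterion is an intraoperative drop-out. These patients are outside the full analysis set and are not at issue here.
- **Stopping the trial intervention.** If continuing would, in the investigator's view, harm the patient, "the investigator may stop the trial intervention for this patient. In this case, the reason for the individual premature trial termination must be recorded". The section does not mention further visits.

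Other parts of the protocol article bear on what follows:

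- Table 2 heads the column for visits 7 to 12 "POM 6, 12, 18, 24, 30, 36 (or pre-mature trial termination". Those visits record DFS, overall survival and local recurrence.
- Section {20c}: "Patients with incomplete observation time due to loss to follow-up or early drop-out will be censored at the last observation". The Primary estimand section has the same rule and labels it a hypothetical strategy. Early drop-out is not defined.
- Primary estimand: "other post-randomisation events (e.g. intervention not as randomised, discontinuation of chemotherapy) will not be considered", which it calls treatment policy.
- Section {20a}: "all randomised patients are included and analysed in the treatment group as randomised".
- Two other departures from the usual course of the operation carry an explicit retention statement. For extended or multi-organ resection: "resection of neighbouring organs are necessary, patients remain in the trial". For delayed reconstruction: "does not result in the exclusion of the patient from the trial".

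**The concern.** The trial intervention is a single phase of one operation, carried out immediately after randomisation. Stopping it means that the allocated dissection is not completed, which is the event that the estimand names and assigns to treatment policy. Section {11b} gives that event a label belonging to the opposite route: termination, no further scheduled visits, censoring.

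The analysis cannot repair this afterwards. Including every randomised patient is formally satisfied by a patient with almost no observation time, but such a patient adds nothing to the comparison. Follow-up that was never collected cannot be restored by an intention-to-treat rule or by a later SAP.

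If patients whose operation is stopped differ in prognosis from the rest, and if stops are not balanced between arms, the confirmatory hazard ratio no longer estimates the treatment-policy effect. Overall survival and local recurrence rely on the same visits and would be affected in the same way.

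**Working it through.** **1. The texts side by side**

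Event: a randomised patient's allocated dissection is stopped.

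| Place | Consequence on its wording |
|---|---|
| {11b} | Called premature termination for that patient; reason recorded |
| Table 2 | Premature termination is an alternative to visits 7 to 12 |
| Primary estimand and {20c}, drop-out rule | If counted as early drop-out: censored at last observation |
| Primary estimand, treatment policy | Event ignored |
| {20a} | Included and analysed as randomised |

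The first three rows form a possible route to early censoring. The last two exclude it. No sentence says which prevails.

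**2. The plan's own event number**

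The Sample size section assumes a "median survival time of 14 months in the control group and 21 months in the treatment group", hazard ratio (HR) 0.667, two-sided 5% and 80% power. Schoenfeld's formula gives

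D = 4(1.960 + 0.842)² / (ln 0.667)² = 191.4, rounded up to 192.

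This reproduces the stated figure. It is used below only to turn an HR into a rejection probability.

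**3. Size if the route were followed (illustration only)**

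From the documents: control median 14 months, so λ = ln 2 / 14 = 0.0495 per month; 36 months of follow-up; 192 events.

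Assumed, because the documents give no figures: a fraction f of each arm has hazard 2λ; all of them are stopped in the TRIANGLE arm and censored at day 0; none is stopped in control; there is no true effect.

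The arms as analysed are then

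- control: S_C(t) = (1−f)e^(−λt) + f·e^(−2λt)
- TRIANGLE: S_E(t) = (1−f)e^(−λt)

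with event densities g_C = −S_C′ and g_E = −S_E′. The large-sample Cox HR θ solves

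∫₀³⁶ [g_E·S_C − θ·g_C·S_E] / (S_C + θ·S_E) dt = 0.

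As a plausibility check at f = 10%, the control hazard starts at 1.1λ against λ in TRIANGLE. The ratio therefore starts at 1/1.1 = 0.91 and moves towards 1 as the high-risk controls have their events.

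The two-sided rejection probability uses the mean shift m = ln(θ)·√192/2. At f = 10%: m = −0.0589 × 6.928 = −0.408, and Φ(−1.960 + 0.408) + Φ(−1.960 − 0.408) = 0.060 + 0.009 = 0.069.

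| f | Patients of 135 | HR under no effect | Two-sided rejection |
|---|---|---|---|
| 2% | 2.7 | 0.99 | 5.1% |
| 5% | 6.75 | 0.97 | 5.5% |
| 10% | 13.5 | 0.94 | 6.9% |

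**4. Sensitivity to the assumptions**

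- f = 10%, with half the comparable controls also stopped: HR 0.97.
- f = 10%, with all comparable controls also stopped: HR 1.00.
- f = 10%, with stops only in control: HR 1/0.943 = 1.06, so the direction reverses.
- f = 10%, HR 0.667 in completed operations and no benefit in stopped patients: following everyone gives 0.69; day-0 censoring in the TRIANGLE arm gives 0.63.

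A second model was simulated with 135 per arm, 36 to 66 months of follow-up and HR 0.667 in the others. Stopped TRIANGLE patients have a median DFS of 6 to 14 months and no matching group in control. Following everyone gives HR 0.68–0.67 at 2% stopped, 0.70–0.68 at 5% and 0.74–0.69 at 10%. Day-0 censoring gives about 0.67 throughout. The shift is 0.00–0.02 at 2% and at most about 0.07 at 10%.

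In that model's setting, expected events at N = 270 fall from 219 to 217, 214 and 209, all above 192. The issue is bias, not loss of events.

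**The case against.** The strongest reply is that {11b} requires only that a reason be recorded. No sentence says that a stopped patient leaves follow-up, none defines a stopped dissection as early drop-out, and Table 2 does not refer to {11b}. The estimand names an operation not done as randomised and ignores it. The additional analyses in {20b} include an as-treated set, which presupposes DFS data on patients who did not receive their allocated operation, and serious adverse events are documented up to visit 12. The article also condenses protocol version 1.0, which may define these terms.

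Much of this stands. The intended analysis is clear, and exit from follow-up is an inference from several places read together. It does not remove the point, because {11b} itself equates stopping the intervention with terminating the trial for that patient, and it lacks the retention sentence given for extended resection and delayed reconstruction. Clear intent in the analysis sections does not tell a site to keep collecting data.

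A reader might go further and infer that stopped patients are censored near day 0, mostly in the TRIANGLE arm, so that the trial is biased in favour of the experimental operation. The documents do not support that:

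- Censoring at day 0 is nowhere stated.
- No stop rate is given for either arm, and the rule applies to both.
- Randomisation follows intraoperative confirmation that both operations are feasible, which should make later stops less frequent.
- Control operations can also fail to be completed as allocated. The control-group section allows deviations only as long as level 3 radicality or triangle clearance is not needed.

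More stops in the longer dissection are plausible, but that is an assumption.

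**Conclusion.** The point holds as a conflict between stated rules. Section {11b}, Table 2 and the undefined early drop-out category permit an early end to follow-up for an event that the estimand and the intention-to-treat rule say must not affect the analysis.

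The size is unknown. If stops occur only in the TRIANGLE arm, with doubled hazard and censoring at day 0, the bias is negligible at a 2% stop rate (null HR about 0.99) and modest at 10% (about 0.94, two-sided error about 7% instead of 5%). It shrinks if controls are stopped too and reverses if stops are mainly in control. The figures show what is at stake; they do not predict the trial's result. The case for acting is that missing follow-up cannot be recovered and the correction is very cheap. The investigator's clinical decision to stop is not judged here.

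**What to change.** Reconcile {11b}, Table 2, the Primary estimand section and {20c} in a few sentences:

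- Stopping or modifying the trial intervention after randomisation does not end trial participation.
- The reason and the operation actually performed are recorded at visit 2.
- The patient continues scheduled follow-up to month 36 and is analysed as randomised.
- Premature trial termination and early drop-out mean only withdrawal of consent to follow-up or loss to follow-up. Both are needed, because the censoring rule already covers loss to follow-up.

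If the full protocol already says this, aligning the wording of {11b} and giving sites matching eCRF guidance is enough. The cost is protocol and eCRF wording, plus a few more patients completing visits that already exist. No clinical rule changes.
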